### Booster and follow-up phone calls

The SMG group facilitator telephones each participant at 12, 16, 22, and 30 weeks after the final group session. During the booster phone calls, facilitators inquire about pain and functioning, current pain management plans, and successes and obstacles in meeting pain management goals, as well as provide encouragement and assistance in problem-solving obstacles encountered in pain management. BOOK participants receive follow-up phone calls at the same intervals to control for attention.

### Steps taken to ensure and monitor group facilitator adherence

Group facilitators are nurses and psychologists with expertise in geriatrics and/or pain management and experience in facilitating therapeutic groups. All are specifically trained according to the treatment protocol. We monitor group facilitator adherence to the self-management group protocol, as recommended by Waltz et al. [26]. All facilitators receive and review a facilitator's syllabus that contains a detailed protocol describing the goals, contents, and activities for each of the 7 sessions. Group facilitators have met 3 times to discuss protocol and treatment integrity issues. Finally, each session for each treatment group is audiotaped. Twenty percent of the audiotapes are randomly chosen and reviewed by a trained research nurse who is not involved in any other aspects of the study. The research nurse listens to the tapes and evaluates the degree to which the group sessions are conducted according to the protocol using a checklist developed for this purpose.

### Measures

Study measures were chosen based on psychometric properties, including sensitivity to change; brevity; and appropriateness for use with community-dwelling, older adults with chronic pain. They are described below and summarized in Table 2.

**Table 2 T2:** Measures and assessment times

**CONSTRUCT/MEASURE**	**SCREENING/BASELINE**	**POST-INTERVENTION**	**6-MONTH FOLLOW-UP**	**12-MONTH FOLLOW-UP**
**Physical Functioning**	√	√	√	√
Roland-Morris Disability Questionnaire				
Brief Pain Inventory (BPI) – pain interference subscale				
**Pain Intensity**	√	√	√	√
Brief Pain Inventory – pain intensity subscale				
**Mood Disturbance/ Social functioning**	√	√		√
Geriatric Depression Scale				
**Pain Beliefs and Coping**	√	√		√
Chronic Pain Coping Inventory – (*includes pain medication use)*				
Coping Strategies Questionnaire – catastrophizing, praying/hoping subscales				
Self-efficacy Scale				
**Pain Knowledge**	√	√		
**Demographics, Medical Conditions, Medications**	√			
Screening & Intake Questionnaire				
Adapted Charlson Index				
**Cognitive Functioning**	√			
Folstein Mini-Mental State Examination				
**Pretreatment Expectations**	√			
**Adherence to Treatment**		√		√
Attendance at classes				
Completion of reading assignments				
Attainment of goals (Personal Pain Management Plan)				

#### Descriptive measures

The following measures are administered at baseline to describe the sample and to explore whether these variables are associated with treatment response. We will compare the two study groups on these measures to determine whether they are comparable at baseline.

##### Screening and intake interview schedule – demographic information and pain history

During the screening process and baseline assessment, participants are asked a series of questions to elicit demographic and pain history variables, including age, race, ethnicity, gender, marital status, education level, sites and duration of pain, and prior and current pain treatments.

##### Folstein mini-mental state examination (MMSE) [27]

The MMSE is a measure that is widely used to assess cognitive function, particularly in older adults. It consists of 30 items, and requires 5–10 minutes to administer. Items assess orientation, memory, attention, and calculation. The MMSE has been demonstrated to be valid and to have good test-retest reliability [28].

##### Charlson index of comorbidity (CI)

The CI is an extensively used, valid, and reliable measure of comorbid medical conditions [29]. The CI uses 19 categories of comorbidity; each category is weighted and scored according to an algorithm [29]. Higher scores indicate greater health burden from comorbid causes. In this study, we are using a self-report version of the CI demonstrated to be reliable and valid in a group of older adults [30]. Because comorbid conditions may be associated with pain appraisal, coping, and outcomes [31], we will examine the association between comorbid conditions and response to therapy.

#### Process measures

##### Self-efficacy scale (SES)

Participants complete the 8-item version of Lorig et al.'s Self- Efficacy Scale [32], which assesses confidence in ability to manage pain and associated problems such as fatigue and negative mood [33,34]. Previous studies have supported the reliability and validity of this measure [32,34,35]. The SES has been tested and used in studies of older adults [36].

##### Coping strategies questionnaire (CSQ) [37]

The CSQ is one of the most widely used measures of pain coping and catastrophizing [38,39]. Measures derived from the CSQ have been shown to be associated with various measures of functioning among patients with different pain conditions [38,40-43]. The CSQ has demonstrated reliability and validity in several samples of older adults, including those who are older than 75 years [44]. For this study, only the catastrophizing and praying/hoping subscales are used. Catastrophizing is included because prior studies have shown that this variable is associated with pain intensity, depression, and disability [45]. The praying/hoping subscale was included because this coping strategy has been found to be associated with the pain experience of older persons[46].

##### Chronic pain coping inventory (CPCI)

The CPCI measures cognitive and behavioral coping strategies used by people to manage chronic pain. It contains 9 subscales: guarding, resting, asking for assistance, relaxation, task persistence, exercise/stretch, seeking support, coping self-statements, and medication use [47]. The CPCI scales have been shown to have acceptable internal consistency and test-retest reliability, and to be associated significantly with physical disability and depression [47-49]. Additional development and psychometric testing have supported the reliability and validity of an additional activity pacing subscale [49].

##### Pretreatment expectations

Prior to learning the study condition to which they are randomized, participants are asked the degree to which they believe that each study condition will be helpful to them. They respond using a 0 to 10 scale, with 0 indicating "not helpful at all" and 10 indicating "extremely helpful."

##### Treatment adherence

1. Class attendance. Group leaders document weekly class attendance. Total attendance is assessed as a percentage of classes the participant attended (out of 7).

2. Reading log/usefulness. Both BOOK and SMG participants complete a form in which they report the amount read on each topic using a 0–5 scale ("I did not look at the section at all" to "I read the section thoroughly"). They also rate the usefulness of each section using a 0–5 scale ("Not at all useful" to "Very useful").

3. Goal attainment. Attainment of SMG participants' pain management goals is assessed using the Personal Pain Management Plan (PPMP). Each week, participants in the SMG group are asked to document the type and frequency of each activity they have chosen to utilize in the management of their chronic pain. They monitor and document the pain management activities that they actually performed over the week. Participants also document obstacles that they have encountered in trying to meet their goals and the solutions they have identified to overcome those obstacles. This form is printed on 2-page paper. The top copy is turned in each week and participants keep the bottom copy for their own records. The PPMP serves several purposes: 1) to assist participants to identify and follow through on their personalized goals; 2) to assess treatment adherence; and 3) to cross-validate data that are collected using the Chronic Pain Coping Inventory.

#### Outcome measures

##### Primary outcome

*Roland-Morris disability questionnaire (RMDQ): *The RMDQ [50] is widely used to assess physical disability associated with low back pain. The RMDQ has been demonstrated to be valid, reliable, and responsive to change [50-55]. Although developed as a measure of physical disability related to back pain, the RMDQ, re-worded without reference to the back, has been found to be a reliable and valid measure of physical disability for patients with other chronic pain problems as well [52]. The RMDQ is scored from 0–24, with higher scores indicating more severe physical disability. Physical disability, as measured by the RMDQ, is the primary study outcome.

##### Secondary outcomes

*Brief pain inventory (BPI): *The BPI is a widely-used, reliable, valid instrument that assesses pain history, location, intensity, and activity interference [56,57]. For this study, pain intensity is measured by calculating the mean of four items in which respondents are asked to rate their average, current, least, and worst pain during the past week, using a scale of 0 ("No pain") to 10 ("Pain as bad as you can imagine"). [58].

Pain-related interference is a composite measure of the degree to which pain limits a person's general function [57]. This variable is calculated as the mean of ratings of pain interference with general activity, mood, walking, work (including housework), relations with others, sleep, and enjoyment of life. Each item is rated on a scale of 0 ("Does not interfere") to 10 ("Completely interferes").

*Geriatric depression scale (GDS): *The GDS [59] is a 30-item self-report measure specifically designed to assess depressive symptoms in older persons. Scores of 11 or higher are considered indicative of depression in older adults. Good sensitivity and specificity for detecting depression in geriatric psychiatric and medical outpatients has been demonstrated (84–100% sensitivity; 73–96% specificity) [60,61]. The GDS was selected over other available depression measures because of its screening efficiency with geriatric outpatient populations, its focus on affective rather than physical symptoms, and its true/false scoring format, which studies have found to be simpler for older adults to complete [61].

### Sample size calculations and statistical analyses

#### Power analysis/sample size calculations

A mixed effects model will be used to analyze data using the participant as the unit of analysis and controlling for baseline value of the outcome as a covariate. A reasonably accurate approximation to this analysis could be obtained by the following procedure: first compute change scores (pre to post) for each person, then collapse to get the mean change score within each site, then do t-tests on these means. This simpler model was used for power calculations, since it allows standard software to be used.

The plan to randomize by site, rather than by individual participant, required additional considerations in calculating statistical power. With this group-randomized design, power depends on the correlation of people within sites, or the *intra-class *correlation. Effect size is defined as the mean change score of all individuals in the intervention group minus the mean change score of all individuals in the control group, divided by the standard deviation of change score within groups. Power calculations for the proposed study are based on estimates of 34 sites (17 intervention and 17 control), 6.4 participants per site (N = 218) providing data at 12 months (20% attrition rate).

Table 3 shows how power (the probability of detecting a difference) varies with the correlation of individuals within site and the effect size. The second column of this table shows the "effective sample size," meaning that the study would have the same power as a study with this sample size and no clustering. If the correlation is zero, the effective sample size is 272, the actual sample size. A correlation of 1 would indicate that all individuals in each site have exactly the same outcome (i.e., no different from having one person per site), so the effective sample size would be 27. Analysis of data from a pilot study showed an intra-class correlation (ICC) of .07 [62]. Although this estimate should be interpreted cautiously because of the limited number of sites in the pilot study, it indicates that the intra-class correlation will probably be fairly small, perhaps 0.05 to 0.1. Our target sample size of 273 enrolled and 20% attrition at 12-month follow-up (yielding a final sample size of 218), assuming ICC=.1, will result in 84% power for detecting an effect size of .5, which Cohen [63] refers to as a "moderate" effect size.

**Table 3 T3:** Power for detecting a difference between the intervention and control group, depending on effect size and intra-class correlation (34 sites, average 6.4 subjects per site)

Intra-class correlation	Effective sample size	Effect size (the difference in means between the two groups, divided by the within-group standard deviation)			
		.40	.50	.60	.70
0.00	218	**84%**	**96%**	**99%**	**100%**
0.05	171	74%	**90%**	**97%**	**100%**
0.10	141	65%	**84%**	**94%**	**98%**
0.20	105	52%	71%	**86%**	**94%**
0.30	83	43%	61%	77%	**88%**
0.50	59	32%	46%	61%	75%
1.00	34	20%	29%	40%	51%

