**Methods/Design:**

This is a randomized, controlled trial to assess the effectiveness of a pain self-management training group intervention, as compared with an education-only control condition. Participants are recruited from retirement communities in the Pacific Northwest of the United States and must be 65 years or older and experience persistent, noncancer pain that limits their activities. The primary outcome is physical disability, as measured by the Roland-Morris Disability Questionnaire. Secondary outcomes are depression (Geriatric Depression Scale), pain intensity (Brief Pain Inventory), and pain-related interference with activities (Brief Pain Inventory). Randomization occurs by facility to minimize cross-contamination between groups. The target sample size is 273 enrolled, which assuming a 20% attrition rate at 12 months, will provide us with 84% power to detect a moderate effect size of .50 for the primary outcome.

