### Recruitment and randomization procedures

Participants are recruited using newsletter announcements, flyers, brochures, and informational talks given at each facility. Retirement community residents who are interested in the study are screened to assess eligibility. Eligible residents who provide written informed consent are then asked to complete the baseline measures and to provide the name of their primary care provider (PCP), as well as permission to contact the PCP. PCPs of SMG group participants are sent a letter about the study and asked to contact the research nurse if there is any medical reason to restrict the resident's participation in the exercise portion of the study.

After all participants from a facility have completed the baseline questionnaires, the facility is randomized to receive either the BOOK or the SMG. Randomization is done by facility, rather than by individual participant, for several reasons. First, it expands the number of participating facilities by making feasible recruitment from smaller facilities. If approximately 5% of residents were recruited from any one facility, then it would not be scientifically or financially sound to involve facilities with fewer than 200 residents in independent or assisted living. A pilot study indicated that the ideal self-management group size is 5–12 participants. If we randomized within facilities, at least 10 participants would need to be recruited from each facility to allow 5 SMG participants. However, if all participants within a facility are randomized to the same condition, then smaller facilities can participate. If more than 12 residents in a facility randomized to the SMG condition enroll in the study, more than one group is scheduled. A second advantage of randomization by facility is that there is little risk of participants in one condition talking with participants randomized to another condition about their experiences in the study. Thus, there is less treatment contamination and likelihood that participants from different conditions will compare treatments, a situation that can provoke dissatisfaction among participants who do not receive the treatment of their choice.

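### Table 3 and the headline 84% power use about 139 degrees of freedom, not the 32 of the t-test on 34 site means said to underlie them; with 32 and equal sites the figure is about 82%

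*Protocol article*

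**What the plan says.** The section on power analysis and sample size calculations in the protocol article plans a participant-level mixed model, but bases power on a simpler stand-in. Change scores are computed per person, and the instruction is to "then collapse to get the mean change score within each site, then do t-tests on these means". The article is explicit that this is where the figures come from: "This simpler model was used for power calculations, since it allows standard software to be used".

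The design inputs are "estimates of 34 sites (17 intervention and 17 control), 6.4 participants per site (N = 218) providing data at 12 months (20% attrition rate". The effective sample size in Table 3 is explained as "meaning that the study would have the same power as a study with this sample size and no clustering". At ICC 0.10 it is 141, and the text says the design "will result in 84% power for detecting an effect size of .5". The abstract repeats that the target enrolment "will provide us with 84% power to detect a moderate effect size of .50 for the primary outcome".

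On site size, the title of Table 3 gives only "34 sites, average 6.4 subjects per site". The recruitment section makes clear that facilities will differ: randomizing whole facilities lets small ones take part, and "If more than 12 residents in a facility randomized to the SMG condition enroll in the study, more than one group is scheduled".

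**The concern.** In a t-test on site means the observations are the 34 means, so the error degrees of freedom are 34 − 2 = 32 whatever the number of people behind each mean. The design effect corrects the variance for clustering. It does not restore the degrees of freedom lost by analysing sites. Reading the effective sample size as an unclustered study of the same size brings in the larger figure unnoticed.

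The table also applies one mean site size throughout. If sizes vary, means from small sites are noisier and power is lower than under equal sizes.

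What is at stake is the accuracy of an unqualified headline that appears in the abstract, the text and the table. Both departures push it in the same direction.

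**Working it through.** **Inputs.** From the power section and Table 3: 34 sites (17 per arm), 6.4 completers per site, N = 34 × 6.4 = 217.6 (printed 218), effect size d = 0.5, ICC = 0.10. The within-group standard deviation of change is the unit of d. The significance level is not stated; two-sided 0.05 is inferred because it reproduces the table.

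**Formulas.** Effective sample size n_eff = N / (1 + (6.4 − 1) × ICC). Power comes from the two-sided noncentral t with noncentrality d × √(n_eff/4).

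**Step 1: reproduce the plan's figure.** n_eff = 217.6 / (1 + 5.4 × 0.10) = 217.6 / 1.54 = 141.3, which matches the printed 141. Noncentrality = 0.5 × √(141.3/4) = 2.97. With df = n_eff − 2 ≈ 139, power is 83.9%, so the printed 84% reproduces.

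**Step 2: identify the table's rule.** The printed n_eff was halved and rounded down to whole people per arm (at ICC 0.10, 70 per arm, df 138, 83.6%). With df equal to the total minus 2, all 28 cells match after rounding. Using 32 df in every row matches 12 of 28, and the normal approximation matches 8. In the ICC = 1 row n_eff is 34 and 34 − 2 = 32, so the two rules coincide there.

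**Step 3: apply the stated method.** Keep the same noncentrality, with 32 df and equal sites:

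| ICC | Effect size | Printed | df = n_eff − 2 | df = 32 |
|---|---|---|---|---|
| 0.00 | 0.40 | 84% | 83.6% | 81.6% |
| 0.05 | 0.40 | 74% | 74.0% | 71.9% |
| 0.10 | 0.50 | 84% | 83.9% | 82.2% |
| 0.20 | 0.50 | 71% | 71.7% | 69.8% |
| 1.00 | 0.50 | 29% | 29.3% | 29.3% |

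The loss in the headline cell is 83.9 − 82.2 = 1.7 points. It shrinks as ICC rises: in the ICC 0.50 row it is at most about 1 point.

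**Step 4: the rest of the protocol's ICC range (32 df, equal sites, d = 0.5).** At the pilot ICC of 0.07, n_eff = 217.6 / 1.378 = 157.9 and power is about 86%. At ICC 0.05, n_eff = 217.6 / 1.27 = 171.3 and power is about 89%.

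**Step 5: unequal site sizes (assumption).** The article gives no coefficient of variation (CV), so these are scenarios at ICC 0.10, d = 0.5 and 32 df. A site with m completers has a mean with variance 0.1 + 0.9/m.

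- Unweighted site means: n_eff = 34 / (0.1 + 0.9 × average of 1/m).
- Optimal weights, close to what a mixed model does: n_eff = 34 × average of m / (1 + 0.1 × (m − 1)).

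| Assumed sizes | Unweighted means | Optimal weights |
|---|---|---|
| Equal | 82.2% | 82.2% |
| CV 0.2 | 81.3% | 81.8% |
| CV 0.3 | 80.2% | 81.4% |
| CV 0.4 | 78.7% | 80.8% |
| CV 0.5 | 76.8% | 80.0% |
| Enrolled evenly over 4–12, 80% retained | 78% | 81% |

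The CV rows for unweighted means approximate the average of 1/m by (1 + CV²)/6.4. Those for optimal weights assume gamma-distributed sizes. The unweighted figures depend on the assumed shape of the size distribution; the weighted ones are more stable.

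**The case against.** The strongest reply is that the effect is small and the t-test is only a stand-in. The part that follows from the article's own inputs is under 2 points, power stays above 80%, and 84% is quoted at the upper end of the expected ICC range of 0.05 to 0.1. The planned mixed model adjusts for baseline and uses three follow-up measurements, and the power calculation credits neither. All of this stands, and it is why the point is minor. It does not remove the mismatch: the article says which test produced its figures, and that test does not give them.

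A reader might infer that true power is nearer 78–81%. The document does not support that as a corrected figure. The 5–12 in the recruitment section is an ideal class size, not a distribution of facility enrolment, and the 4–12 spread used above is an assumption. The 78% end also belongs to an unweighted test that the trial does not plan to run.

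A reader might also infer that the group test itself will have inflated type I error. That would follow only if participant-level degrees of freedom were used in the mixed model. The statistical analysis section does not choose a method for these, and an analysis plan commonly settles it, so this is not a finding.

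**Conclusion.** The point holds as a minor arithmetic correction. The stated method has 32 degrees of freedom, while Table 3 uses about 139 at ICC 0.10. With 32 degrees of freedom and equal sites, the headline is about 82% rather than 84%. This rests on the article's own inputs plus an inferred two-sided 5% level.

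The effect of unequal sites cannot be fixed from the document. As a sensitivity range it is about 80–82% with mixed-model-type weighting for a CV up to 0.5, and about 78% for unweighted means under the assumed 4–12 spread. At the pilot ICC of 0.07, which the article itself treats with caution, equal-site power is about 86%. The adequacy of the sample size is not in question.

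**What to change.** - Recompute Table 3 with 32 degrees of freedom in every row.
- Restate 84% as about 82% (ICC 0.1, effect size 0.5, equal sites) in the abstract, the power section and Table 3.
- Add one labelled sensitivity line for unequal site sizes with the assumed CV stated, preferably the CV seen in enrolment so far.
- Note beside it that baseline adjustment and repeated measures are not credited, and that equal-site power is about 86% at the pilot ICC.
- In the same edit, reconcile the effective sample sizes of 272 (ICC 0) and 27 (ICC 1) in the text with the 218 and 34 in Table 3.

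The cost is slightly less favourable printed figures. No change in enrolment or in the planned analysis is needed.
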